#### Participant timeline

4.7.1

Refer to Figure 5 for the SPIRIT figure of the participant timeline.

**Figure 5 fig5:**
[figure not shown]
SPIRIT figure of participant timeline.

#### Recruitment

4.7.2

Recruitment takes place at the Integrative Health Center, Tung Wah College, and Squina International Center for Infection Control. These centers are well-equipped with fit testing devices and simulated clinical environments for performing CPR. The devices and facilities have been accredited and used for practical examination by the Hong Kong Nursing Council.

### Assignment of interventions: allocation

4.8

#### Sequence generation

4.8.1

The randomization process will be conducted using computer-generated randomization by a research nurse to determine random allocation, that is the sequence of donning the respirators in this crossover design. All participants will receive an anonymous identifying number to ensure anonymity.

Participants will be randomized with equal probability (1:1 ratio). The block sizes will not be disclosed to ensure concealment.

#### Concealment

4.8.2

Participants will be randomized using sealed envelopes. Only the research nurse who generated the allocation sequence knows the order of randomization.

#### Implementation

4.8.3

Participants are randomly allocated to either the group using a traditional respirator or to the group using the new respirator according to an allocation sequence prepared by the research nurse before the start of the study.

### Assignment of interventions: blinding

4.9

#### Who will be blinded

4.9.1

The research team member assigned to perform data input is blinded to the allocation sequence.

#### Procedure for unblinding if needed

4.9.2

Not applicable.

## Data collection and management

5

### Plans for assessment and collection of outcomes

5.1

The plan for the collection of outcomes is illustrated in Figure 2 and the measurements are described in the abovementioned section of “Outcomes.”

### Plans to promote participant retention and complete follow-up

5.2

Once a participant is enrolled or randomized, the principal investigator will ensure reasonable effort to follow the participant through the study period.

Participants may withdraw from the study for any reason at any time, without consequences. Participants may also withdraw if the study sponsor or organization sponsoring the trial terminates the study before the proposed end date. Participants who complete the trial are provided with HK$300 (~US$38) incentive as time compensation.

### Data management

5.3

All data recorded are stored and backed up on an encrypted hard drive. Data entry and management will be completed by one of the research team members and double-checked by a minimum of one other team member. Personal identifiers will be removed upon completion of the study and stored for long-term retention of the research data. Data will be retained for at least 7 years.

### Confidentiality

5.4

Participant and study-related information will be securely stored at the study site with limited access. All data collection and administrative forms will be coded to maintain participant confidentiality. Personal identifiers, such as informed consent forms will be removed from the local database and stored separately from participant information.

### Plans for collection, laboratory evaluation and storage of biological specimens for genetic or molecular analysis in this trial/future use

5.5

Not applicable.

## Statistical methods

6

### Statistical methods for primary and secondary outcomes

6.1

Statistical Package for the Social Sciences (SPSS) version 27 will be used to perform descriptive and inferential statistical analysis. Descriptive statistics, including mean, standard deviation, percentage, and frequency, will be used to report the demographics, fit rate, and mask usability. The intention-to-treat (ITT) principle will be applied. We expect no carry-over and no period effect for this study based on previous experience. Chi-square test for categorical variables and independent sample t-test for continuous variables will be used to examine comparability among groups by randomization. Independent sample *t*-tests and paired *t*-tests will be used to compare real-time leakage among different groups of tested respirators during procedure, before and after procedures, respectively. Generalized estimating equations (GEE) will be used to evaluate the total real-time leakage difference in the interaction of time and cycles of chest compression. All the tests will be two-sided, and a *p*-value will be set at 0.05 for statistical significance.

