### Trial design

3.1

The study is a randomized controlled, exploratory crossover trial with two arms (*n* = 100 in each arm) to examine and compare the real-time leakage of traditional and new respirators during two standard clinical procedures (i.e., nasopharyngeal suctioning and CPR).

The study will employ two sequential phases. A cross-sectional exploratory design in phase 1 will investigate the fit rate and usability of three types of respirators (two traditional melt-blown respirators with head-loop design and one new nano-respirator with ear-loop and clips) among Chinese HCWs, which is used to identify potential participants for the next phase. A cross-sectional design is appropriate to estimate the prevalence of unfit respirators through testing in a group of large samples.

Phase 2 is a randomized controlled crossover trial with two arms: participants donned with traditional best-fit respirators (either 1860S or 1870+), and participants donned with a new respirator (made of nanomaterial and ear-loop with clip design). A best-fit respirator refers to a given respirator obtaining the highest fit factor when donned by a user. A crossover design has advantages over a parallel experiment because the participating subject will act as his or her control, and possible incomparability between “intervention” and “control groups” could be eliminated. A two-arm study can yield reliable evidence about the effectiveness of real-time protection between traditional and new respirators. Randomization is performed as block randomization with a 1:1 allocation. To protect participants’ rights, anonymity, and confidentiality, the study was designed with the ethical principles of the Declaration of Helsinki. The paper complies with the SPIRIT recommendation for study protocol (25). The overall CONSORT flowchart of the study design is shown in Figure 1.

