#### Intervention description

4.5.2

Eligible participants are randomly allocated in equal proportion to either control or intervention (traditional or new respirator group). New respirator as intervention has been illustrated and described in Figure 3. Standard scenarios are introduced to participants in advance to reduce stress from the environment and psychological factors. Sufficient time is provided for participants to familiarize themselves with the devices and settings. Participants are required to don all necessary personal protective equipment (assigned N95 respirators, gown, and face shield) for nasopharyngeal suctioning and CPR in the designated simulation environment. Data of real-time leakage is recorded at 30 s intervals during the nasopharyngeal suctioning and CPR. After 2 min suctioning (15 s for two times) and a 4 min one-person CPR, participants donned with the tested respirator will perform fit testing and respond to mask usability, which is recorded as data of post-procedure. With a 10 min rest, participants will don another respirator and repeat the measurement of real-time leakage (i.e., crossover), fit test, and usability.

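### The primary respirator contrast is assigned an independent-sample t-test although every participant wears both respirators, so its p-values and confidence intervals are invalid unless the within-person correlation is zero

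*Protocol article*

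**What the plan says.** Real-time leakage during nasopharyngeal suctioning and CPR is the primary outcome (sections 2.1.1 and 4.6.1). It is measured repeatedly: "Data of real-time leakage is recorded at 30 s intervals during the nasopharyngeal suctioning and CPR".

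The design is within-person. Section 3.1 justifies the crossover on the ground that "the participating subject will act as his or her control". Section 4.5.2 has the first respirator followed by a short rest, after which "participants will don another respirator and repeat the measurement of real-time leakage (i.e., crossover), fit test, and usability". Section 4.8.1 says that what is randomised is "random allocation, that is the sequence of donning the respirators in this crossover design".

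The analysis sentence in section 6.1 reads "Independent sample *t*-tests and paired *t*-tests will be used to compare real-time leakage among different groups of tested respirators during procedure", and its closing words are "among different groups of tested respirators during procedure, before and after procedures, respectively". Two tests and two comparisons are thus matched in order: the independent-sample test goes to respirator groups during the procedure, and the paired test goes to before versus after. The next sentence plans GEE for leakage over time and cycles of chest compression. The same section expects neither carry-over nor a period effect. All tests are two-sided at 0.05.

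**The concern.** The two sets of leakage readings being compared come from the same people, so they cannot be assumed independent. A test that ignores the pairing computes its standard error as if two separate groups had been measured. That removes the advantage for which section 3.1 chose the crossover.

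If people who leak more in one respirator also tend to leak more in the other (positive rho), the estimated difference is unaffected, but its interval is too wide and its p-value too large. The direction matters here. Section 3 hypothesises that leakage does not differ significantly between respirators, so an over-conservative test leans toward the trial's own hypothesis. Section 8 intends the results to inform purchasing and possible replacement of traditional models, where a missed difference could be read as equal protection.

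**Working it through.** **Inputs from the protocol article.** Effect 0.40, power 80%, two-sided 5%, total 200 (section 4.7); 100 per arm (section 3.1); every participant wears both respirators (sections 3.1, 4.5.2, 4.8.1). The type of effect size is not stated; I take 0.40 as a difference in SD units.

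**Assumption.** The within-person correlation rho between a participant's leakage in the two respirators is not given. I show 0, 0.3, 0.5 and 0.7, with equal SDs and one summary value per participant per respirator.

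**Step 1: the plan's own figure.** For two independent groups, n per arm = 2 × (1.96 + 0.842)² / 0.40² = 98.1, so 99; the t-based value is 99.08, so 100 per arm and 200 in total. The stated 200 is reproduced, with power 80.4% at 100 per arm. A paired calculation for the same 0.40 SD gives 51–52 participants at rho = 0.5. The sample size therefore matches a parallel-group calculation, as does the test in section 6.1.

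**Step 2: standard errors with 200 people wearing both** (in SD units).
- Used by the independent test: √(2/200) = 0.100.
- Correct for the within-person difference: √(2(1 − rho)/200), which is 0.0837, 0.0707 and 0.0548 for rho 0.3, 0.5 and 0.7.
- Ratio: 1/√(1 − rho).

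**Step 3: consequences.**
- True type I error = 2 × [1 − Φ(1.96/√(1 − rho))].
- Power of the independent test = Φ((δ − 1.96 × 0.100)/SE correct).
- Power of the paired test = Φ(δ/SE correct − 1.96).

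Example at rho = 0.5, δ = 0.20: independent Φ(0.004/0.0707) = 52%; paired Φ(2.83 − 1.96) = 81%.

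| rho (assumed) | CI width ÷ correct width | True type I error | Power at 0.20 SD, independent | Power at 0.20 SD, paired | Power at 0.40 SD, independent |
|---|---|---|---|---|---|
| 0 | 1.00 | 5.0% | 52% | 52% | 98% |
| 0.3 | 1.20 | 1.9% | 52% | 67% | 99.3% |
| 0.5 | 1.41 | 0.6% | 52% | 81% | 99.8% |
| 0.7 | 1.83 | 0.03% | 53% | 95% | >99.9% |

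Simulation with 20,000 trials per rho agreed on type I error: 1.9%, 0.6% and 0.03% for the independent test, and close to 5% for the paired test. At a negative rho of −0.2 the error reverses and the type I error is about 7.4%.

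**The case against.** **GEE is planned for the same outcome and handles correlated data.** This is true, but the sentence targets time and compression cycles and names no respirator effect. It also cannot cover suctioning, which has no compressions. It does not replace the t-test for the primary contrast.

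**The sentence is loosely worded, and the paired test may be meant for the respirators.** On its plain reading it says the opposite. If it is merely loose, the primary test is undetermined and the same sentence needs correcting.

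**The independent test might be meant for the first wear only, 100 against 100.** That would be valid, with power of about 80% at 0.40 SD. It would discard half the data, however, and power at 0.20 SD would be about 29%: Φ(0.20/√(2/100) − 1.96). Nothing in section 6.1 restricts the comparison this way.

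**The error is conservative and costs almost nothing at the design effect.** This stands. A reader might infer that the trial is underpowered. It is not for the planned 0.40 SD, because 200 readings per respirator give about 98% power even at rho = 0. The 0.20 SD used to show the loss is half the planned effect.

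**The repeated 30 s readings.** A reader might also infer that these will be entered as separate rows, which would inflate false positives. The documents do not say so. Section 4.6.1 only counts the readings collected, and section 6.1 names GEE for leakage over time. I make no claim on that point.

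**Conclusion.** The concern holds. As written, section 6.1 assigns the primary contrast a test whose independence assumption the design contradicts. The p-value and interval are invalid whenever rho is not zero. For positive rho both err on the conservative side, by the amounts tabulated above.

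The size of the error rests wholly on rho, which the documents do not give; at rho = 0 the two tests agree. The harm is wrong inference and lost precision for differences smaller than planned, in a trial whose hypothesis is the absence of a significant difference. It is not a bias in the estimated difference or a shortage of power at 0.40 SD.

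**What to change.** In section 6.1, replace the independent-sample t-test for the respirator contrast by a within-participant analysis, done separately for suctioning and for CPR. Either of these would serve:
- a paired t-test on each participant's mean leakage per respirator within that procedure; or
- a mixed model or GEE clustered on participant, with respirator and period terms, which also accommodates the repeated 30 s readings.

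Report the new-minus-traditional difference with its 95% confidence interval. Keep the procedures apart, because section 4.6.1 collects 4 readings in a 2-minute procedure and 8 in a 4-minute one. Pooling all readings would weight CPR two to one, although the objective concerns both procedures.

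The cost is one sentence and standard SPSS procedures, with no new data. Section 8.1 says the trial is completed but its results have not been disseminated, so the change can be made and recorded before reporting.

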#### Primary objective

2.1.1

To compare real-time leakage by using traditional and N95 respirators during two clinical procedures, which are nasopharyngeal suctioning and CPR.

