#### Strategies to improve adherence to interventions and scenarios

4.5.4

A face-to-face adherence session will take place at the designated simulated environments. This will include:Instruction to the standardization of N95 respirator-wearing protocol (Figure 2).Importance of following instructions for standard scenarios and measurements of the speed and depth of chest compression to ensure minimal discrepancy.Instruction about the duration of suctioning (i.e., two times suctioning for a maximum of 15 s each) and one-man CPR (a total of 4 min, which included two series of five cycles) (Figure 2).

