#### Primary outcome measures

4.6.1

Real-time leakage will be measured by portable aerosol spectrometers (Grimm Model 1.109-006 and 007; Grimm Technologies, Ainring, Germany) during two selected clinical procedures. They will provide rapid measurement of particle concentration with optical sizes of 0.25–0.32 μm and different sizes from 31 channels. The system will consist of two spectrometers, the first will measure ambient air particle concentration, and the second will measure air particle concentration inside the respirator. This device will be placed on a designated table throughout the assessment. Participants will perform real-time measurements for real-time leakage at an average of 30 s intervals while performing the standard clinical procedures. A total of eight sets of data are collected within a 4 min procedure while 4 sets of data are collected in a 2-min one. Portable aerosol spectrometers have been used to measure real-time leakage during aerosol-generating procedures and some nursing procedures, namely, open suctioning, nasogastric-tube insertion, and napkin change (15, 16).

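### The only repeated-measures model targets a time-by-compression-cycle interaction that cannot answer traditional versus new, and the respirator comparison is left to unpaired t-tests with no single primary contrast

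*Protocol article*

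**What the plan says.** The primary objective (section 2.1.1) is "To compare real-time leakage by using traditional and N95 respirators during two clinical procedures, which are nasopharyngeal suctioning and CPR". Section 4.6.1 fixes a leakage reading every 30 s: "A total of eight sets of data are collected within a 4 min procedure", and four in the 2-minute suctioning. That makes 12 readings per wear. Section 4.5.4 describes the CPR task as "a total of 4 min, which included two series of five cycles".

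Section 6.1 assigns the analysis of leakage to two kinds of method:

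- Independent-sample and paired t-tests, which "will be used to compare real-time leakage among different groups of tested respirators during procedure, before and after procedures, respectively". Read in order, the independent-sample test goes with the comparison during the procedure and the paired test with the comparison before and after.
- A GEE: "Generalized estimating equations (GEE) will be used to evaluate the total real-time leakage difference in the interaction of time and cycles of chest compression".

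The section adds that "All the tests will be two-sided" and that the p-value "will be set at 0.05 for statistical significance". It does not say which comparison, procedure or summary of the readings is primary. Section 3.1 justifies the crossover on the ground that each participant is his or her own control.

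**The concern.** The GEE is the one stated method that could use all repeated readings and respect the clustering within participants. The effect named for it is not a respirator effect. An interaction of time with cycle number asks how leakage evolves during CPR. It does not ask whether leakage differs between traditional and new respirators. Suctioning, one of the two procedures in the primary objective, has no compressions, so no such term exists for it.

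The respirator question therefore rests on the t-tests. The one assigned to the procedures themselves is the unpaired version, which discards the advantage the crossover was chosen for. Two procedures imply at least two such comparisons, and nothing says which of them decides the trial. Section 8 links the results to purchasing policy and to possible replacement of all traditional models, so the deciding comparison should be unambiguous.

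**Working it through.** **Inputs from the protocol article.** Effect 0.40, power 80%, 5% level and total 200 (section 4.7); 100 per arm (section 3.1); two-sided tests (section 6.1); eight CPR and four suctioning readings at 30 s intervals (section 4.6.1); ten cycles in 4 min (section 4.5.4). **Assumed, because not given:** a steady compression pace, the within-person correlation between wears, and the correlation between tests.

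**1. The plan's own figure.** For two independent groups, n per arm = 2(1.96 + 0.8416)²/0.40² = 98.1, so 99 per arm and 198 in total. The t-based version gives 99.08, so 100 per arm and 200 in total. The stated 200 reproduces as an unpaired comparison.

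**2. Time against cycle number.** 240 s / 10 cycles = 24 s per cycle. Readings end at 30, 60, …, 240 s. The cycle in progress, the ceiling of t/24, is 2, 3, 4, 5, 7, 8, 9, 10. Sums of squares about the mean are 37,800 for time and 60 for cycle, with cross-product 1,500. So r = 1,500/√(37,800 × 60) = 0.996. The product time × cycle correlates 0.999 with time squared. If cycles means the first or second series of five, the correlation with time is 0.87.

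**3. Unpaired test on both wears of the same people.** Let ρ be the within-person correlation. The unpaired standard error ignores ρ, so under no difference the statistic has variance of about 1 − ρ, and the true level is P(|Z| > 1.96/√(1 − ρ)).

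| ρ (assumed) | Effective cut-off | True level |
|---|---|---|
| 0.3 | 1.96/0.837 = 2.34 | 1.9% |
| 0.5 | 1.96/0.707 = 2.77 | 0.6% |

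Simulation with 200 participants gave 1.8% and 0.5%.

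**4. What that costs in power.** With 200 people in both wears, the unpaired statistic has mean d/√(2/200) and standard deviation √(1 − ρ). The paired statistic has that mean divided by √(1 − ρ), and standard deviation 1. At ρ = 0.5:

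- d = 0.40: the mean is 4. Unpaired power is Φ((4 − 1.96)/0.707) = 99.8%, and paired power is above 99.9%.
- d = 0.20 (illustrative): the mean is 2. Unpaired power is Φ(0.04/0.707) = 52%, and paired power is Φ(2.83 − 1.96) = 81%.

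At ρ = 0.3 and d = 0.20 the figures are 52% and 67%. In sample-size terms, a paired analysis of d = 0.40 needs 71 participants at ρ = 0.3 or 52 at ρ = 0.5, against about 100 per arm unpaired.

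**5. Two procedures, each at 0.05, with correctly sized tests.** Independent tests give 1 − 0.95² = 9.75%. At correlation 0.5 between the tests the figure is about 9.1%, and at 0.8 it is 7.8%.

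**The case against.** The strongest reply is that the GEE sentence is a condensed line in a journal article, not a list of model terms. Its word for difference may well mean the difference between respirators, since the sentence before it compares respirator groups. On that reading the GEE is a supplementary look at CPR dynamics, and leaving out suctioning is not an error in itself. The primary question still has a stated type of test, the t-test, which matches the sample size. This stands in part: the document shows only that a respirator effect is not named, not that none would be fitted. But even on the generous reading, the named interaction tests whether the respirator difference changes over CPR, not whether it is zero.

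Three stronger inferences should be resisted.

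- A reader might infer that the interaction cannot be identified. It can. As a near-quadratic in time it is estimable from eight readings; it is simply not a respirator contrast. The 0.996 also depends on a steady pace and on time meaning elapsed seconds, which the section does not define.
- A reader might compute false-positive rates for 12 separate intervals (46% if independent) or for 31 size channels. The article describes these as measurements and nowhere says that each is tested. Such figures are conditional on a plan it does not state.
- A reader might conclude that the t-tests inflate false positives. If both wears enter an unpaired test, the opposite is likelier: two tests at 1.9% sum to at most 3.8%. Inflation arises only if the tests are correctly sized, for example when 100 people per arm are compared on the first wear alone.

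The article also calls the trial exploratory, which softens the multiplicity point but not the mismatch between model and objective.

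**Conclusion.** The point holds. The effect named for the only repeated-measures model does not answer the primary objective and cannot cover suctioning; neither statement depends on an assumed number. The closeness of the interaction to a curvature term rests on a steady pace (0.996, or 0.87 for the two series).

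The comparison during procedures is stated as an unpaired test in a crossover. If both wears are used, its true level is about 1.9% at an assumed within-person correlation of 0.3 and 0.6% at 0.5. The harm is lost power: negligible at the planning effect of 0.40 with all 200 people in both wears, but substantial for smaller differences. If the tests are correctly sized instead, two unadjusted procedure tests give 7.8% to 9.8% familywise error. The article does not say which data enter the test, so its error rate is unsettled in either direction. No single primary contrast is named under either reading.

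**What to change.** Replace the GEE and t-test wording for leakage with one GEE or mixed model:

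- **Outcome:** concentration inside the respirator relative to ambient, in one stated particle-size range.
- **Data:** all 12 readings of both wears, clustered on participant.
- **Terms:** respirator, procedure, interval within procedure, respirator × interval, period and sequence.
- **Primary test:** the respirator effect averaged over the readings, as the sole test at 0.05. Equal weight per reading gives CPR and suctioning weights of 8 and 4; state the weights intended.
- **Secondary:** the suctioning and CPR effects, tested with Holm's method.
- **Descriptive only:** results by interval, size channel and CPR series. The time-by-cycle interaction is dropped.

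No new data are needed. One cost is a slightly stricter threshold for procedure-specific claims. The other is procedural: section 8.1 reports the trial as completed with results not disseminated, so the change must be dated and disclosed, with a statement of who had seen which data when it was made.
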